## Abstract

*Background*: Community-based initiatives show promise for preventing childhood obesity. They are characterized by community leaders and members working together to address complex local drivers of energy balance. *Objectives*: To present a protocol for a stepped wedge cluster randomized trial in ten communities in the Great South Coast Region of Victoria, Australia to test whether it is possible to: (1) strengthen community action for childhood obesity prevention, and (2) measure the impact of increased action on risk factors for childhood obesity. *Methods:* The WHO STOPS intervention involves a facilitated community engagement process that: creates an agreed systems map of childhood obesity causes for a community; identifies intervention opportunities through leveraging the dynamic aspects of the system; and, converts these understandings into community-built, systems-oriented action plans. Ten communities will be randomized (1:1) to intervention or control in year one and all communities will be included by year three. The primary outcome is childhood obesity prevalence among grade two (ages 7–8 y), grade four (9–10 y) and grade six (11–12 y) students measured using our established community-led monitoring system (69% school and 93% student participation rate in government and independent schools). An additional group of 13 external communities from other regions of Victoria with no specific interventions will provide an external comparison. These communities will also allow us to assess diffusion of the intervention to control communities during the first three years of the trial. *Conclusion*: This trial will test effectiveness, over a five-year period, of community-owned, -supported and -led strategies designed to address complex and dynamic causes of childhood obesity.

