### 1.1. A Sustainable Monitoring System

In 2015, a childhood obesity-monitoring system was established across six local government areas in South-Western Victoria [17]. We used locally sourced competitive funding to conduct training, manage data collection, conduct analysis and support an in-kind contribution from health services, local government and schools to conduct data collection. Anthropometric and behavioural data were collected from 90% of children in 48 of the 84 primary schools in the GSCRV. Partners have committed to provide in-kind support to collect these data again in 2017 and 2019.

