## 2. Methods

This is a cluster randomized stepped wedge trial (two steps) in ten communities. The unit of randomisation and intervention is the community (rather than individual children). Following baseline measurement of all eligible children in all ten communities (2015), five communities will be randomized to the intervention in year one (step one) and the remaining five will be entered into the intervention two years later (step two) (Table 1). Grades two, four and six children in all clusters will be measured in the baseline year (2015), year two (2017) and year four (2019). Data collection every second year reflects a more cost-effective measurement approach and a realistic timeframe to begin to see changes in weight status among intervention populations. Opportunities and funding for longer-term data collection (i.e., a five- and ten-year follow up) will be actively sought in due course.

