### 2.7. Sample Size

Based on school enrolment data, we estimate that there are 5050 children in the GSCRV in grades two, four or six across 84 primary schools in the region. Using an opt-out consent process, which delivers a >90% response rate, and assuming that 75% of schools will participate, we expect to measure more than 3000 children at each study wave meaning 3000 observations at each step and 9000 across the three study data points. BMI-z standard deviation (1.2) and intra-cluster correlation (0.027) were estimated in a previous study of >2500 Victorian school children (2014–2015). Under the stepped wedge design (ten clusters, three data collection points, five clusters) randomized to intervention at step 1, there will be an average of 300 children in each cluster, and the minimum detectable difference in BMI-z between groups with 80% power will be 0.13. This compares favourably with the observed difference achieved in previous successful intervention studies in children of 0.18, which was associated with a 3% reduction in prevalence of overweight and obesity over three years [7,8,9].

While the power for the current study is based on the stepped wedge design alone, the external parallel control group of 13 communities will add an additional comparative power to this trial.

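### The detectable difference of 0.13 matches the article's inputs only under an unstated one-sided 5% test, and the assumed school participation exceeds that of the 2015 baseline

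*Protocol article*

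**What the plan says.** Section 2.7 (Sample Size) takes a BMI-z standard deviation of 1.2 and an intra-cluster correlation of 0.027 from an earlier Victorian study. It describes the design as "Under the stepped wedge design (ten clusters, three data collection points, five clusters) randomized to intervention at step 1", says that "there will be an average of 300 children in each cluster", counts "3000 observations at each step and 9000 across the three study data points", and concludes that "the minimum detectable difference in BMI-z between groups with 80% power will be 0.13". It compares this with a difference of 0.18 seen in earlier successful studies. Neither this section nor any other gives a significance level or says whether the test is one- or two-sided.

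Section 2 (Methods) fixes the crossover: "five communities will be randomized to the intervention in year one (step one) and the remaining five will be entered into the intervention two years" after the first five. Measurement falls in 2015, 2017 and 2019. Section 3 (Analysis Plan) names a linear mixed model whose only random effect is community.

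On yield, Section 2.7 starts from 5050 children in 84 schools and writes, "assuming that 75% of schools will participate, we expect to measure more than 3000 children at each study wave". Section 1.1 reports that in 2015 data were "collected from 90% of children in 48 of the 84 primary schools in the GSCRV". The Abstract gives a different rate: "69% school and 93% student participation rate in government and independent schools".

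**The concern.** A detectable difference quoted at 80% power with no further qualification will be read as referring to a two-sided 5% test. On that reading 0.13 is too small for the inputs printed beside it, and the margin below the 0.18 benchmark looks wider than it is. If a one-sided test was meant, the figure depends on a choice that the reader cannot see.

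The sample-size input raises a separate question. The 2015 baseline is the first of the three analysed waves and had already been collected, with a share of schools well below the share assumed for every wave.

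**Working it through.** **Inputs.** From Section 2.7: SD 1.2, ICC 0.027, m = 300 per community and wave, 80% power. From Section 2 and Table 1: I = 10 communities and T = 3 waves, with five communities following the pattern 0,1,1 and five following 0,0,1. From Section 3: community random effect and fixed wave effects. My assumptions: independent samples at each wave, equal community sizes, a single intervention effect (no time-by-intervention term), and a normal reference distribution.

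**Variance components.**
- Between communities: t = 1.44 × 0.027 = 0.03888
- Within, per community-wave mean: s = 1.44 × 0.973 / 300 = 0.00467

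**Design sums.**
- U (treated cells) = 5×2 + 5×1 = 15
- W (squared wave totals) = 0² + 5² + 10² = 125
- V (squared community totals) = 5×4 + 5×1 = 25

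**Hussey-Hughes variance.**
Var = I·s·(s + T·t) / [(I·U − W)·s + (U² + I·T·U − T·W − I·V)·t]
- Numerator: 10 × 0.0046704 × (0.0046704 + 0.11664) = 0.005666
- Denominator: (150 − 125) × 0.0046704 + (225 + 450 − 375 − 250) × 0.03888 = 0.1168 + 1.944 = 2.0608
- Var = 0.002749, SE = 0.0524

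**Reproducing the article's figure.** One-sided 5%: (1.645 + 0.842) × 0.0524 = 0.130, and power at 0.13 is 79.8%. This matches.

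**Two-sided 5%.** (1.960 + 0.842) × 0.0524 = 0.147. Power at 0.13 is Φ(0.13/0.0524 − 1.960) = 69.8%. Power at 0.18 is 93%.

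**Two-sided variants under the same model.** None gives 0.13 at the stated inputs:
- SD read as the within-community SD: 0.149
- full yield, 5050 × 0.75 × 0.90 = 3409, or 341 per community: 0.138
- ICC of zero: 0.123, so 0.13 would need an ICC close to zero
- size needed for 0.13: about 385 children per community and wave

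**Participation.** 48/84 = 57%. If the participating schools are of average size, 5050 × 48/84 × 0.90 = 2597 children, or about 260 per community.

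| Children per community and wave | SE | One-sided 5%: detectable difference (power at 0.13) | Two-sided 5%: detectable difference (power at 0.13) | Two-sided power at 0.18 |
|---|---|---|---|---|
| 300 | 0.0524 | 0.130 (80%) | 0.147 (70%) | 93% |
| 260 in all waves | 0.0563 | 0.140 (75%) | 0.158 (64%) | 89% |
| 260 in 2015, 300 later | 0.0530 | 0.132 (79%) | 0.149 (69%) | 92% |

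The last row uses the same model with unequal wave sizes, solved by generalised least squares.

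**The case against.** Four points can be made for the article.

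1. **Alpha is simply not printed.** A one-sided 5% test reproduces 0.13 almost exactly, so the article contains no demonstrable arithmetic error. This stands, and it is why the point concerns an undisclosed choice and not a miscalculation.

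2. **The same children recur.** With grades two, four and six measured every second year, up to two-thirds of children are shared between adjacent waves and one-third between the first and last. If the analysis credits a within-child correlation (given community), the two-sided figure at 300 falls to 0.129 at a correlation of 0.3 and to 0.116 at 0.5. At 260, a correlation of 0.4 gives 0.132. So a two-sided test could also reach 0.13. However, the article states no such correlation, and the model in Section 3 has a random effect for community only. Unequal community sizes, decay of the community correlation over time and small-sample corrections, all ignored here, push the other way. The rescue therefore also depends on something undisclosed.

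3. **The 75% is labelled an assumption and leaves slack.** 75% × 90% × 5050 = 3409, while the power calculation uses 3000. Reaching 3000 needs only 3000/(5050 × 0.90) = 66% of schools. School sizes are not given, so a share of schools is not a share of children: the 48 schools would reach 3000 if they averaged about 15% more eligible pupils than the regional mean. Schools are also re-invited at each wave. All this limits the precision of the 2,600, but 57% is below 66% as well as below 75%. The Abstract's 69% does not settle the matter, because it covers government and independent schools only, whereas the 5050 children are spread over all 84.

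4. **Adequacy against 0.18 survives.** It does, in every row of the table.

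A reader might also infer that a null result would be taken as excluding 0.13. The article makes no such claim, and the confidence interval would govern that reading.

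**Conclusion.** The point holds in a limited form. Under independent samples per wave and the community random effect of Section 3, 0.13 at 80% power corresponds to a one-sided 5% test that the article never states. A two-sided 5% test gives about 0.147, with 70% power at 0.13. The 75% school share and 3000 children per wave conflict with the 57% of schools reported for 2015. If that participation persists and participating schools are of average size, 0.13 is missed under either sidedness in this model (0.140 or 0.158). If only the baseline wave falls short, the loss is small (0.132 or 0.149).

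Two stronger readings are tempting. One is that 0.13 cannot follow from the article's inputs; it can, because alpha and sidedness are left open. The other is that the trial is underpowered for its benchmark; it is not on these figures, since two-sided power at 0.18 is about 93% with 300 per community and 89% with 260. The margin below 0.18 is overstated on a two-sided reading, but the adequacy conclusion is not overturned. The severity is moderate.

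**What to change.** In Section 2.7:

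- State the significance level, the sidedness and the variance formula, and any within-child correlation credited to repeat measurement. If such a correlation is credited, make the model in Section 3 agree with it.
- If the test is two-sided 5% with independent samples, restate the detectable difference as about 0.15 at 3000 children per wave. If it is one-sided, say so beside the 0.13.
- Replace the 75% and 3000 inputs by the schools and children actually measured in 2015, or show both. On the average-size assumption this gives about 0.16 two-sided or 0.14 one-sided; the actual 2015 count would remove that assumption.
- Reconcile the 57% implied by Section 1.1 with the 69% in the Abstract by giving the denominator for each.

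The cost is text only. No design, sample or procedure changes. If the test is two-sided, the published figure becomes somewhat less favourable but stays below 0.18.

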### 2.8. Environmental Audits

Environmental audits will be conducted using a modified version of the Schools’ Environmental Audit survey [46] including elements of the international study of childhood obesity, lifestyle and the environment (ISCOLE) survey [46].

### 2.9. Ethics Approvals

Full ethics clearances have been received for all methods described above: Deakin University’s Human Research Ethics Committee (DU-HREC) 2014-279, DU-HREC 2013-095, Deakin University’s Human Ethics Advisory Group-Health (HEAG-H) HEAG-H 194_2014, HEAG-H 17 2015, HEAG-H 155_2014), the Victorian Department of Education and Training 2015_002622, 2013_002013, and the Catholic Archdiocese of Melbourne, Sale, Sandhurst and Ballarat.

## 3. Analysis Plan

Social network analysis (SNA) [47] will be used to quantify the strength and importance of relationships among people and organizations who have control over environments that affect children’s health [48]. Social network analysis software (e.g., “SNA” and “network” in R [49] will be used to calculate network statistics for each community including density and centrality and “opinion leader” positions, which are statistics used to identify people in the network who send or receive the most connections to others (the former indicating influence, the latter prominence), or who occupy other central or bridging positions in a network that are important to network diffusion and connecting relatively disconnected areas of the network. Social network dynamics will be modeled using longitudinal network models to determine how the networks change over time, the factors that predict the formation and maintenance of new relationships, and the role of the network in the diffusion information, knowledge and practice. Additional systems measurement will comprise evaluation of change in systems maps, tracking of change in subsystems and process evaluation of the communities’ responses to the systems intervention. The grounded logic models developed through this process will also allow the addition of other data sources, whether bespoke or routine data, for an understanding of the change in systems.

The effect of the intervention on the main outcome (BMI-z) will be assessed using a linear mixed model with cluster as a random effect (community) and time (step), intervention and interaction of time by intervention as fixed effects. Because intervention enrolment will be staggered, data will be analyzed following two different approaches: (1) an intention to treat principle irrespective of when the enrolment effectively occurred; and (2) considering actual enrolment time. Secondary outcomes will be analyzed by fitting a generalized linear mixed model with link and distribution selected according to the variable (Figure 2). Missing outcomes (which we anticipate will be sparse due to the selection criteria “child present at school on the day of data collection”) will be managed using an inverse probability weighting approach.

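### The primary BMI-z model names community as its only random effect, so its standard error and the stated minimum detectable difference rest on two unsupported assumptions that pull in opposite directions

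*Protocol article*

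**What the plan says.** Section 3 (Analysis Plan) specifies the primary BMI-z model as "a linear mixed model with cluster as a random effect (community"), with "time (step), intervention and interaction of time by intervention as fixed effects". No community-by-wave, school or child term is named.

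Section 2 (Methods) gives the design: "five communities will be randomized to the intervention in year one (step one) and the remaining five will be entered into the intervention two years" after the first five. Grades two, four and six are "measured in the baseline year (2015), year two (2017) and year four (2019"). Section 2.6 has schools recruited afresh in each of those years.

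Section 2.7 (Sample Size) states that "BMI-z standard deviation (1.2) and intra-cluster correlation (0.027) were estimated in a previous study of >2500 Victorian school children (2014–2015"), that "there will be an average of 300 children in each cluster", and that this means "3000 observations at each step and 9000 across the three study data points". It concludes that 0.13 BMI-z is detectable with 80% power and compares this with an effect of 0.18 seen in earlier studies. It gives no between-wave correlation, within-child correlation, significance level or sidedness.

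**The concern.** All ten communities are untreated in 2015 and, by Table 1, all are under intervention in 2019. The treatment effect is therefore estimated largely from change within communities. Two sources of variation act on exactly that contrast, and a lone community intercept ignores both.

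- **Community-by-wave variation.** One intercept makes two children from the same community as alike four years apart as within one wave. Communities may drift, and a changing set of participating schools adds to this. Omitting it makes the SE too small.
- **Recurring children.** A grade-two child in 2015 is due in grade four in 2017 and grade six in 2019. The model treats those measurements as independent given community. Omitting the child-level correlation makes the SE too large.

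The coverage of the primary confidence interval, its type I error and the detectable difference all depend on the balance between the two. The ICC is described as coming from a single 2014–2015 study, which as described cannot show what happens between waves.

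**Working it through.** **Inputs from the protocol.** 10 communities, 3 waves, 5 crossing over before wave 2 and 5 before wave 3; 300 children per community per wave; SD 1.2; ICC 0.027. **Assumptions, not in the documents:** CAC 0.8 to 0.95; within-child correlation ρ 0.6 to 0.9. Calculations are on community-by-wave means with a single treatment effect and normal quantiles.

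**Variances.** Total 1.2² = 1.44. Community 0.027 × 1.44 = 0.03888. Child 1.44 − 0.03888 = 1.40112, which is 1.40112/300 = 0.00467 for a mean of 300.

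**Step 1: reproduce the stated figure.** Under the stated model, the covariance of a community's three means is V_m = 0.03888·J + 0.00467·I (J all ones, I identity). With D_i holding three wave indicators and the treatment indicator, the generalised least squares variance is the treatment element of (Σ D_i′V_m⁻¹D_i)⁻¹, giving SE = 0.0524.
- Two-sided 5%: (1.960 + 0.842) × 0.0524 = 0.147.
- One-sided 5%: (1.645 + 0.842) × 0.0524 = 0.130.

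So 0.13 is reproduced at CAC 1 with 300 per community only if the test is one-sided. Two-sided with 0.75 × 5050/10 = 379 children per community gives 0.131. The step from 0.13 to 0.147 is therefore a matter of alpha or sample size, not of random effects.

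**Step 2: add community-by-wave variance, total ICC fixed.** V_t = 0.03888·CAC·J + [0.03888·(1 − CAC) + 0.00467]·I. The added variance is 0.0019, 0.0039 and 0.0078 at CAC 0.95, 0.9 and 0.8, against 0.0047 from sampling children. The true variance of the stated model's estimate is A⁻¹BA⁻¹, with A = Σ D_i′V_m⁻¹D_i and B = Σ D_i′V_m⁻¹V_tV_m⁻¹D_i. Type I error is 2Φ(−1.96/ratio), where ratio is true SE over model SE.

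**Step 3: add recurring children.** With three grades two years apart, up to two-thirds of children recur between consecutive waves and one-third between 2015 and 2019. Full overlap adds 0.00467·ρ·(2/3) or 0.00467·ρ·(1/3) to the matching off-diagonal elements of V_t.

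Results (the model's own SE stays at 0.0524; the MDD is two-sided 5%, 80% power, using weights from the correct covariance; overlap columns run from ρ = 0.6 to 0.9):

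| CAC | Ratio, independent | Type I | MDD | Ratio, full overlap | Type I | MDD |
|---|---|---|---|---|---|---|
| 1 | 1.00 | 5% | 0.147 | 0.74–0.57 | below 1% | 0.11–0.08 |
| 0.95 | 1.19 | 10% | 0.174 | 0.98–0.85 | 4.5–2% | 0.144–0.125 |
| 0.9 | 1.35 | 15% | 0.197 | 1.17–1.07 | 9–7% | 0.171–0.157 |
| 0.8 | 1.62 | 23% | 0.235 | 1.48–1.40 | 18–16% | 0.215–0.204 |

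A 150-run mixed-model simulation with independent children rejected the null in 6%, 14% and 22% of runs at CAC 1, 0.9 and 0.8. Coding separate effects by duration of exposure instead of one effect gives ratios of 1.18, 1.34 and 1.60.

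**Step 4: schools.** Assume school variance of 1–3% of the total and 0.75 × 84/10 = 6.3 schools per community. If the same schools appear at every wave, omitting the school term leaves the SE ratio at 0.985–0.995. If only half of the school component carries over between waves, the ratio is 1.11–1.30.

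**The case against.** The strongest case against is that a reader might infer from the missing community-by-wave term that the SE is too small and the power statement fails. The documents do not support that as a certainty. The grade structure makes many children recur, and with strong within-child correlation the excess type I error disappears at CAC 0.95 and is modest at 0.9. If only 75% of those children are re-measured, the ratios at CAC 0.95 are about 1.03 to 0.95. The direction depends on two quantities that the protocol does not give. This objection stands and limits the point.

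Two further tempting readings also fail. The omission of schools as such is not a source of error: a stable school effect largely cancels in within-community change, and only turnover or school-by-wave variation matters. Section 2.6 makes turnover possible but no turnover figure is given. Nor is the whole distance from 0.13 to the recalculated MDDs due to the random effects, since two-sided testing at 300 per community already gives 0.147.

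It can also be said that an article condenses, and that variance terms and degrees of freedom may be in an analysis plan not shown. That is fair for the degrees-of-freedom method. It carries less weight for the random part, because the article states a structure and rests its power claim on a single ICC.

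**Conclusion.** The point holds in a limited form. As stated, the model gives a valid SE only if between-wave correlation is perfect and recurring children are uncorrelated, or if the two errors happen to cancel. Over the assumed ranges, the true SE lies between 0.85 and 1.62 times the reported one for CAC 0.95 to 0.8. The nominal 5% test then has a true level of about 2% to 23%. At CAC 0.8 it is anti-conservative under every overlap assumption examined (16% to 23%).

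The MDD carries the same uncertainty. Over CAC 0.95 to 0.8 it is about 0.17–0.24 with independent children and 0.13–0.22 with full overlap, two-sided. It exceeds the 0.18 benchmark at CAC 0.9 with independent children and at 0.8 in either case, but not at 0.95. The favourable comparison in section 2.7 is therefore neither confirmed nor refuted.

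These sizes depend on the assumed CAC and within-child correlation, on the ICC of 0.027 applying to communities (its level is not stated), and on normal quantiles. Small-sample degrees of freedom for ten clusters would raise the MDDs somewhat.

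**What to change.** Specify random effects for community, community-by-wave and child, plus school and school-by-wave where they can be estimated, with Kenward-Roger or Satterthwaite degrees of freedom for ten clusters. The child term requires that records can be linked across waves; say whether they can.

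Restate the MDD over a range of CAC (for example 0.8 to 1) and of within-child correlation, with alpha, sidedness, children per community and the level of the ICC given.

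The cost is a somewhat more complex model, with probably wider intervals and a less favourable MDD. No additional measurement is needed.

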### 2.1. Study Population

The units of observation are all primary school-aged children in grades two, four and six (aged approximately 6 to 12 years) (*n* = 5050) in ten communities of the GSCRV. Clusters, or “natural communities”, are distinct, dispersed population centres agreed by partners based on existing government, health service, and education boundaries (see Figure 1). The ten enrolled clusters will be ranked in order of size, and one community from each quintile will be randomly allocated to intervention at step one. Blinding and allocation concealment is not possible in trials where whole communities are recruited into the design, implementation and evaluation.

This stepped wedge design [18,19] is particularly suited to situations where: randomisation of individuals is not possible (i.e., population level trials); the intervention is expected to be of benefit and unlikely to do any harm (i.e., where previous small-scale interventions have been successful); and, where allocation of communities to a control-only arm would be problematic, unethical, or likely to result in communities refusing to participate [20,21]. The design provides strong analytic qualities, with intervention/control exposure and comparison available both within and across arms [22,23]. The trial described requires intensive support efforts across multiple communities and so it is not feasible to deliver it across all communities simultaneously. It is also designed iteratively so that subsequent communities benefit from lessons learned from the preceding communities.

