### 2.6. Procedures

In Term 1 of each study year (2015 baseline, 2017 and 2019) presentations will be made to school principal networks (agreed partners), with written invitations and an information pack sent to each school principal, followed up with phone calls and/or personal visits to recruit schools. Assembly and classroom presentations will be made to all children in the target grades regarding the study, at which time the Plain Language Statement and opt-out consent form will be distributed. All children in each target grade will be enrolled unless they return an opt-out consent form signed by their parents/guardians or opt out verbally. Measurements will typically be conducted over a one-day visit to each school in the second term of each year (March to June). A team of up to six trained data collectors (all with current Working with Children Checks or equivalent) will collect anthropometric and survey data in one class period. Data collectors will be trained by study leads in anthropometric measurement, accelerometer fitting, questionnaire delivery and sensitivity when engaging young children.

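### The plan calls missing outcomes sparse by counting only children present on the day, while its own figures leave a third to a half of the target children unmeasured, mainly through school non-participation that could differ by arm

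*Protocol article*

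**What the plan says.** Section 2.1 of the protocol article sets the target: "The units of observation are all primary school-aged children in grades two, four and six", with n = 5050 in the ten communities. Section 2.7 gives the source of that number: "we estimate that there are 5050 children in the GSCRV in grades two, four or six across 84 primary schools in the region". Section 2.4.3 then narrows participants to children available at their school on the day whose parents have not opted them out, and section 2.5 limits measurement to consenting schools.

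The Analysis Plan (section 3) states "Missing outcomes (which we anticipate will be sparse due to the selection criteria", names presence at school on the day as that criterion, and assigns the missing outcomes to inverse probability weighting. It does not say which children form the denominator of the weights. The primary model has community as its only named random effect, with time, intervention and their interaction as fixed effects.

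The article reports coverage in three places:
- Section 2.7, for planning: "assuming that 75% of schools will participate, we expect to measure more than 3000 children at each study wave". The child response within those schools is put at more than 90% under opt-out consent.
- Section 1.1, for 2015: "Anthropometric and behavioural data were collected from 90% of children in 48 of the 84 primary schools in the GSCRV".
- The abstract: 69% of schools and 93% of students, for government and independent schools.

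Section 2.6 repeats school recruitment in each study year, with invitations "followed up with phone calls and/or personal visits to recruit schools". Section 2.1 says that neither blinding nor allocation concealment is possible.

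**The concern.** Missingness looks small in section 3 because unmeasured children are placed outside the group in which it is counted. A child in a school that declines has no BMI-z. That child belongs to the section 2.1 population but, on the natural reading of section 3, is not a missing outcome and gets no representation through the weights.

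Low coverage that is stable over time mainly limits generalisability. The comparison between arms is at risk if coverage changes differently by arm. Randomisation follows the 2015 baseline, so the 2015 set of schools cannot have responded to allocation. The 2017 and 2019 sets can: schools are approached again when allocation is known, and section 2.2 describes an intervention that works through local leaders, including those in education. If schools join or leave at different rates in the two arms, and those schools differ in BMI-z, the community means by wave move for a reason other than the intervention. A random effect for community that is constant over time does not absorb such a movement, and weights built for absence on the day do not address it.

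**Working it through.** **Inputs.** 5050 children and 84 schools (section 2.7); 75% of schools and 90% of children, the latter the stated lower bound (section 2.7); 69% and 93% (abstract); 48 of 84 schools and 90% of children (section 1.1); SD 1.2, intra-cluster correlation 0.027 and detectable difference 0.13 (section 2.7).

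**The plan's own figure first.** Coverage = school share × child response. With the planning inputs, 0.75 × 0.90 = 0.675, and 0.675 × 5050 = 3409. This agrees with the stated expectation of more than 3000 per wave.

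**Share of the 5050 without an outcome.** Unmeasured share = 1 − coverage. The part due to schools is 1 − school share. The part due to children within participating schools is school share × (1 − response).

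| Basis | Measured | Unmeasured | From schools | From children within schools |
|---|---|---|---|---|
| Planning: 0.75 × 0.90 | 67.5% (3409) | 32.5% | 25.0 points | 7.5 points |
| Abstract: 0.69 × 0.93 | 64.2% (3241) | 35.8% | 31.0 points | 4.8 points |
| Power basis: 3000/5050 | 59.4% (3000) | 40.6% | not separable | not separable |
| 2015: 48/84 × 0.90 | 51.4% (2597) | 48.6% | 42.9 points | 5.7 points |

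Every row except the power basis treats the share of schools as the share of children, because enrolment by school is not given. If declining schools are small, the true unmeasured share is lower in those rows.

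**How far the arm mean could move (illustration only).** Suppose school participation rises from 48/84 = 57.1% to 75% in one arm and stays unchanged in the other.
- Share of that arm's sample from new schools: (0.75 − 0.571)/0.75 = 0.238.
- Between-cluster SD: 1.2 × √0.027 = 0.197. The article does not say whether this correlation refers to schools or communities, so using it as a between-school SD is an assumption.
- Worst case, all new schools one SD away in the same direction: 0.238 × 0.197 = 0.047 BMI-z, and 0.047/0.13 = 36% of the detectable difference.
- Half that gap: 0.047/2 = about 0.023, or 18% of 0.13.
- New schools differing independently: with 42 schools per arm (84/2, equal split assumed), 42 × 0.179 = 7.5 are new, and the typical shift is 0.238 × 0.197/√7.5 = 0.017, or 13% of 0.13. This is random variation, not a systematic bias.

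**The case against.** The strongest reply is that non-participation and a missing outcome in a participant are different things. Section 2.4.3 defines participants as those available on the day, section 2.5 refers to consenting schools, and section 2.7 openly allows for 75% of schools. Among children so defined, sparse missingness is a fair expectation. How the weights are built is also a matter that an article may leave to a statistical analysis plan, and none is shown. This stands in part: the article does not say that the weights exclude everyone else. That is the natural reading of section 3, not its text.

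Three stronger inferences are tempting, and the documents do not support them.
- *That the presence rule itself leaves a third to a half unmeasured.* It does not. School non-participation accounts for 25 to 43 points; absence and opt-out add about 5 to 8. Nor does presence guarantee an outcome, since section 2.6 lets a child opt out verbally.
- *That the move from 57% to 75% shows that the school set will change, and differently by arm.* The denominators may differ. If the 48 schools are also the abstract's 69% (an assumption), that denominator is 48/0.69, about 70 schools, with about 14 outside it. Part of the apparent rise could then be one sector joining across the region. A change common to both arms is absorbed by the fixed effect for time.
- *That the effect estimate is biased by about a third of the detectable difference.* The 0.047 assumes a one-arm rise with every new school a full SD away in one direction. Nothing in the article says that new schools differ systematically.

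The reply leaves the central point untouched: nothing fixed in section 3 would deal with school entry or exit that differs by arm after open allocation.

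**Conclusion.** The point holds in a limited form, as a cheap improvement. Against the section 2.1 population, the article's own figures put the unmeasured share between 32.5% and 48.6%, mostly from schools that do not take part. Describing missing outcomes as sparse is defensible only within participating schools. Because schools are recruited again after open allocation, participation could diverge by arm, and the stated model and the natural reading of the weighting would not correct for that.

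The size of any bias cannot be determined from the article. The illustrations run from about 0.02 BMI-z to about 0.05 in a one-arm worst case, against 0.13. They rest on school share standing for child share, on the 0.027 correlation describing differences between schools, and on an assumed imbalance between arms. Whether such an imbalance will arise is unknown.

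**What to change.** 1. Delete the statement that missing outcomes will be sparse, or limit it to children within participating schools.
2. Define coverage against school enrolment, and report school and child participation by arm and wave.
3. Add a school-participation stage to the inverse probability weights, at least as a sensitivity analysis. Use school-level variables obtainable for all 84 schools: community, sector, enrolment size and earlier participation. The article mentions school enrolment data but does not show that grade-by-sex rolls are held for declining schools, so this stage should not depend on them.
4. Add a sensitivity analysis restricted to schools measured in both 2015 and 2017, and a further one requiring 2019 as well. State its limit: it reduces bias from newly joining schools but still conditions on participation after allocation, so it does not exclude bias from schools dropping out differently by arm.

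The cost is analysis wording, assembly of a few school-level variables, and somewhat larger standard errors from unequal weights and from the smaller restricted sample. No change to data collection from children is needed.
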